## Abstract

**Background:**

As demand for Emergency Department (ED) services continues to exceed increases explained by population growth, strategies to reduce ED presentations are being explored. The concept of ambulance paramedics providing an alternative model of care to the current default ‘see and transport to ED’ has intuitive appeal and has been implemented in several locations around the world. The premise is that for certain non-critically ill patients, the Extended Care Paramedic (ECP) can either ‘see and treat’ or ‘see and refer’ to another primary or community care practitioner, rather than transport to hospital. However, there has been little rigorous investigation of which types of patients can be safely identified and managed in the community, or the impact of ECPs on ED attendance.

**Methods/Design:**

St John Ambulance Western Australia paramedics will indicate on the electronic patient care record (e-PCR) of patients attended in the Perth metropolitan area if they consider them to be suitable to be managed in the community. ‘Follow-up’ will examine these patients using ED data to determine the patient’s disposition from the ED. A clinical panel will then develop a protocol to identify those patients who can be safely managed in the community. Paramedics will then assess patients against the derived ECP protocols and identify those deemed suitable to ‘see and treat’ or ‘see and refer’. The ED disposition (and other clinical outcomes) of these ‘ECP protocol identified’ patients will enable us to assess whether it would have been appropriate to manage these patients in the community. We will also ‘track’ re-presentations to EDs within seven days of the initial presentation. This is a ‘virtual experiment’ with no direct involvement of patients or changes in clinical practice. A systems modelling approach will be used to assess the likely impact on ED crowding.

**Discussion:**

To date the efficacy, cost-effectiveness and safety of alternative community-based models of emergency care have not been rigorously investigated. This study will inform the development of ECP protocols through the identification of types of patient presentation that can be considered both safe and appropriate for paramedics to manage in the community.

## Background

Emergency Department (ED) crowding (and access block) has been described as the most serious issue currently confronting EDs [1-3]. The demand for ED services exceeds any growth that can be explained by population increase [4]. A recent Australian Institute of Health and Welfare (AIHW) report identified that “between 2009–10 and 2010–11, ED presentations increased in all states and territories, with increases ranging from 1.6% in Tasmania to 8.1% in Western Australia” [5], p vii. ED crowding has been linked to a range of adverse outcomes for patients and staff, including increased medical errors, increased patient mortality, patient dissatisfaction, high levels of work-related stress, decreased morale among ED staff and decreased capacity of EDs to respond to mass casualty incidents [2,3,6,7].

Ambulance usage is also increasing annually. In Western Australia (WA), St John Ambulance Western Australia (SJA-WA) activity in the Perth metropolitan area increased by 23% to 171,462 cases attended in the 2010/11 financial year from138,996 cases in 2006/07 [8]. For the year 2012, SJA-WA paramedic crews in metropolitan Perth attended a total of 132,862 cases and 105,327 (79.3%) were transported to ED. (“unpublished data” provided to [name] by SJA-WA.) Increasing numbers of ambulance arrivals are one of the key drivers of ED demand and also increased episodes of ramping [9]. There is growing recognition that not all patients attended by paramedics actually need to be transported to ED. As part of a major overhaul of emergency services in the UK [10], the concept of ‘emergency care practitioners’ (EmCPs) emerged as an alternative model of ambulance paramedic response [10-12]. Initial reports showed that EmCPs were dealing with “54% of patients without the need for an immediate referral to another healthcare professional or emergency transportation to ED” [11]. A cluster randomised trial in the UK reported reduced ED attendance associated with Paramedic Practitioner (a similar role to EmCP) attendance, whilst maintaining patient satisfaction and safety [13].

Notwithstanding reports of the apparent success of the EmCP role in the UK, the structure of the health system, both in relation to primary care and emergency services, is different to that in both Australia and New Zealand. Extended care paramedics (ECPs) have been introduced in New Zealand [14], NSW [15] and SA [16]. In 2009 the Wellington (New Zealand) Ambulance service initiated a new model of care for a rural district with approximately 50,000 residents and a high proportion of over 65 year olds. Ambulance staff, trained in additional clinical skills, are sent to patients with conditions considered amenable to treatment in their own homes or local communities [14]. As explained, “this has shifted the focus of the ambulance service towards taking healthcare to the patient and away from automatically transporting the majority of patients to hospital” [14, p11]. A recent paper [17] reports favourable results for the first 1,000 patients attended by ECPs, with 40% of patients transported to the ED when compared to 74% of patients attended by conventional ambulance crews. Moreover, only 5% of patients who had been managed in the community by an ECP had an acute ED presentation within 7 days of that ECP attendance; although no comparison data were provided for conventional ambulance crews.

In the Sydney West-Nepean catchment area, the ECP program commenced operations in December 2007. By October 2009, a total of 22 ECPs had responded to over 10,000 cases, with a non-transport rate of 38% - 45% depending on area [15]. The South Australian Ambulance Service (SAAS) introduced an ECP programme in the metropolitan area in December 2008 [16]. A conference abstract reported that in the first 7 months “ECPs attended 1123 patients, of those 555 interventions (49.4%) were considered to have prevented an ED presentation and 60 (5.3%), were considered to have prevented a hospital admission; and no adverse events were recorded” [18].

ECPs provide alternative care pathways for patients who call for an ambulance and meet certain pre-defined criteria, such as the patient having a minor illness or injury, or only requiring basic medical advice or reassurance [15]. Through a ‘see and treat’ or a ‘see and refer’ strategy it is suggested that they can assist in reducing ambulance transport to hospital [16]. Whilst there is clear enthusiasm about the concept of ECPs as an alternative community-based model of emergency/primary health care, there is no good quality research data in Australia to support the efficacy, safety or cost-effectiveness of an ECP programme. It needs to be established that patients seen by ECPs do not end up presenting to ED within hours/days of the initial ECP attendance – possibly in a worse clinical condition than their initial presentation – or come to harm or die because of an unrecognised life-threatening condition.

Our project will develop and test (through simulation) the feasibility and safety of empirically derived clinical protocols for an extended care paramedic (ECP) role for the Perth metropolitan area. We are aware of the fact that paramedics do not have the same repertoire of clinical assessment skills as emergency physicians, nor do they have access to the same array of diagnostic tests. Of concern to all clinicians is the risk of failing to identify potentially catastrophic events, such as sepsis, stroke or myocardial infarction. Thus, while we are interested in modelling the impact of the introduction of ECPs on ED demand and ED crowding, our primary concern will be patient safety.

## Methods/Design

### Setting

Perth is located in the south-western corner of Australia. It is the capital city of WA and has a land area of 5,400 km^2^[19]. The estimated population for the Perth Statistical Division in 2011 was 1,728,867 persons [20] of whom 49.6% were men and the median age was 36 years.

### Ambulance services in WA

All road-based emergency ambulance services in WA are provided by a single ambulance service provider, St John Ambulance (Western Australia) [21]. Emergency phone calls (‘000’) for an ambulance are received by the ambulance service operations centre and computer-aided dispatch (CAD) used to assign calls to ambulance paramedic crews. During the study period, patient care data will be recorded by the paramedics using the existing electronic patient care record (e-PCR). The e-PCR data are linked to the CAD data for each episode of care.

### Emergency departments in Perth

Within the Perth metropolitan area, there are 11 Emergency Departments – 10 in public hospitals and one in a private hospital [22]. There are approximately 580,000 attendances to these EDs per annum, leading to about 170,000 admissions to hospital [23].

### Data collection

During the study period, we will include e-PCR and CAD data from SJA-WA and Emergency Department Information System (EDIS) [24] data for patients transported to the public hospital EDs [24], supplemented with hospital medical record review for a sample of patients. EDIS is a computerised patient tracking system used by the EDs in Perth to collect clinical, demographic and administrative data. Patients transported to the private hospital (without EDIS) will be manually tracked.

For the medical record review component of the study we will select a sample of patients identified as being suitable for management in the community and a research nurse will extract data from the in-hospital medical records to determine the diagnostic tests and clinical procedures performed and patient outcomes.

### Ethics approval

No direct involvement of patients is required and there will be no change in actual clinical practice in this study. Human Research Ethics Approval has been obtained from the University of Western Australia (#RA/4/1/5514), with waiver of informed consent. We also have human research ethics approval to follow-up a sample of patients at three tertiary teaching hospitals in Perth: Sir Charles Gairdner Hospital, Royal Perth Hospital, Fremantle Hospital, and the private hospital St John of God - Murdoch. This may be extended to include other hospitals depending on the findings from the initial phase of the study.

### Research plan

The study will be conducted in several consecutive phases, as follows:

### Phase 1: Collect baseline data

Over a 3 month period, we will include all patients within the Perth metropolitan area attended by SJA-WA paramedics and transported to one of the11 Perth EDs. The paramedics will routinely indicate on the e-PCR whether, in their opinion, they consider that the patient they attended could have *potentially* been managed by an ‘extended care paramedic’ through either a) ‘see and treat’ , or b) ‘see and refer’ strategies. (All paramedics will be emailed a clinical circular outlining the process for indicating on the e-PCR the possible alternative pathways.) In addition, the details of any patients attended by SJA-WA paramedics but not transported to ED (currently recorded as ‘Ambulance Not Required’ - ANR) will also be captured as part of the study.

The ED disposition and other clinical outcomes of the patients in this study cohort will be obtained via the WA EDIS data, WA hospital data and WA death registry data. Further clinical information about diagnostic tests performed and the principal reason for the patient’s admission to hospital or discharge from the ED will be abstracted from medical record reviews for a sample of patients.

The characteristics of the patients identified as potential candidates for non-transport to ED will be compared to those who were flagged as requiring transport to ED, with respect to:

a. Age, gender, socioeconomic status (based on residential address), geographical location, residential care facility, pre-hospital clinical problem code, ambulance dispatch priority code, time of day, day of week (SJA-WA data).

b. The Australasian Triage Score (ATS) [25] and presenting complaint recorded in ED.

c. ED diagnosis; ED disposition (discharge home; admit; died) and time in ED.

d. For those admitted to hospital: diagnosis, length of stay, procedures, disposition.

e. For all patients: representation at ED (or ambulance attendance) within 24 hours; 48 hours and within one week of the initial ambulance attendance.

f. A random sample of patients identified as being able to be managed in the community (proportionately across each hospital and major diagnosis category) will have medical record review by the study research nurse, to determine the nature of the clinical care received.

### Phase 2: Development of ‘trial’ ECP clinical protocols

A clinical reference group will be established with study investigators and clinical/community stakeholders (including paramedics). Based on the findings gained from Phase 1 of the study together with the best available evidence, clinical protocols for patients who could either be a) seen and treated on scene by a paramedic or b) referred to another community service will be developed. This phase of the study will involve an iterative process of refinement (through face-to-face meetings and document review) of the clinical protocols for the appropriate identification and management of patients under the extended scope of paramedic practice model of care (ECPs).

### Phase 3: Test the ECP protocols (simulation)

Following the development of clinical protocols for ECPs in Perth, a second 3-month cohort of SJA-WA patients will be studied. For this cohort, paramedics will routinely identify (on the e-PCR) whether the patient that they attended met the defined clinical protocol criteria for management by an ECP through either a) ‘see and treat’, or b) ‘see and refer’ strategies. Patient outcomes will be followed up, as described for Phase 1 of the study, to again compare the demographic, clinical characteristics, ED disposition and re-presentation at ED or readmission to hospital.

### Phase 4: Refinement of the ECP protocols

The clinical reference group will be reconvened to review the data from Phase 3 to determine the safety and appropriateness of the alternative paramedic pathway for the management of patients flagged as suitable for non-transport to ED and to refine the clinical protocols as required.

### Phase 5 – Education/training requirements

An educational reference group will review the findings from Phase 3 of the study, to determine the additional knowledge and skills that would be required for SJA-WA paramedics to undertake the required extended scope of practice. An appropriate reference group for this task will include representation from the SJA-WA College Educators, SJA-WA paramedics, University Academics, Emergency Medicine clinicians and community stakeholders.

### Phase 6: Economic evaluation

The costs of providing emergency care to patients treated in accordance with current practice (where the majority of paramedic attendances results in transport to ED), will be compared with the costs of care provided under a new model incorporating an ECP. Cost estimation will include costs incurred by the ambulance service, community health services and hospitals providing ED and inpatient care. Unit costs will be obtained from hospitals, ambulance and community services. We will initially scope the data collected in Phase 3 to assess if it is feasible to estimate the average cost of care provided for each patient contact. This would involve the use of patient level data relating to ED diagnosis, time in ED, hospital admission length of stay and procedures undertaken to calculate the average cost per patient under the current model of care (treatment provided in ED). For each contact flagged as potentially being managed by an ECP, we will estimate the cost to provide treatment using either ambulance or community services. This will allow for an estimation of the average cost of treatment under an ECP model of care. We will compare the average cost of care under current practice and the new ECP model to identify any cost savings that may offset the upfront costs of providing a training programme to the ambulance service.

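### As described, the ECP-side cost in Phase 6 has no place for returns to ED or readmissions, so the saving is overstated if non-transport raises 7-day returns

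*Protocol article*

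**What the plan says.** The protocol article, under Phase 6 (Economic evaluation), opens with a broad cost perspective: "Cost estimation will include costs incurred by the ambulance service, community health services and hospitals providing ED and inpatient care". It then describes the calculation, starting with a scoping step on the Phase 3 data to "assess if it is feasible to estimate the average cost of care provided for each patient contact".

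- **Current practice.** The average cost is to be built from "patient level data relating to ED diagnosis, time in ED, hospital admission length of stay and procedures undertaken".
- **ECP model.** For each flagged contact, "we will estimate the cost to provide treatment using either ambulance or community services". The next sentence says that this yields the average treatment cost under the ECP model.

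The two averages are compared to find savings that might offset the cost of training. No time horizon is given.

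Elsewhere the article does collect later events. Phase 1, item e, records for all patients "representation at ED (or ambulance attendance) within 24 hours; 48 hours and within one week of the initial ambulance attendance". Phase 3, whose data feed the costing, follows "ED disposition and re-presentation at ED or readmission to hospital".

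**The concern.** The Background treats early ED attendance after ECP care as something that has to be ruled out, and the study tracks returns for a week. Yet the ECP-side cost is defined by two kinds of service, ambulance and community, and a later ED visit or readmission is neither. On the current-practice side the listed items could cover a second visit, but re-presentation is not named.

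The comparison therefore sets a cheaper first contact against ED care and does not charge the ECP model when community management fails. If failure is more frequent after non-transport than after ED care, the error favours ECP, and it falls on the figure to be weighed against training costs. Phase 7 models service use and ED demand but states no costs, so it does not fill the gap.

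**Working it through.** The article states no unit cost, saving or return rate for the Perth cohort, so there is no figure to reproduce. The check sets the cost definitions beside the outcomes collected, then uses a simple identity to see what matters.

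**Step 1: where a return would be costed.**

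| Event within 7 days | Collected? | Named in current-practice items? | Within the ECP-side definition? |
|---|---|---|---|
| ED re-presentation | Yes (Phases 1 and 3) | No | No |
| Readmission | Yes (Phase 3) | No | No |
| Repeat ambulance attendance | Yes (Phase 1, item e) | No | Only as a separate contact |

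The last row does not rescue the calculation. In a per-contact average, a repeat attendance enters the denominator as a new contact and is not charged to the first decision. A patient who returns without an ambulance is not an ambulance contact at all.

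**Step 2: the identity.** Per flagged patient, set the index cost under current practice to 1. Let *k* be the relative cost of an ECP contact, *m* the relative cost of a return (taken as equal in both models), *r1* the 7-day return rate under ECP, *r0* the rate after ED care, and *r* = *r1* − *r0*.

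- Saving without returns: 1 − *k*
- Saving with returns: (1 + *r0·m*) − (*k* + *r1·m*) = (1 − *k*) − *r·m*
- Share of the saving lost: *r·m* / (1 − *k*)
- Break-even excess rate: *r\** = (1 − *k*) / *m*

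Only the excess matters. If *r1* = *r0*, the returns cancel and the saving is unchanged. If *r1* < *r0*, leaving returns out understates the saving.

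**Step 3: illustration.** All values of *k* and *m* are assumptions, and so is an excess of 5 percentage points. For example, with *k* = 0.5 and *m* = 3: 0.05 × 3 / 0.5 = 30%, and *r\** = 0.5 / 3 = 16.7%.

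| *k* | *m* | Share lost, *r* = 5 points | Share lost, *r* = 2.5 points | Break-even excess |
|---|---|---|---|---|
| 0.3 | 1 | 7.1% | 3.6% | 70% |
| 0.3 | 3 | 21.4% | 10.7% | 23.3% |
| 0.3 | 5 | 35.7% | 17.9% | 14% |
| 0.5 | 1 | 10% | 5% | 50% |
| 0.5 | 3 | 30% | 15% | 16.7% |
| 0.5 | 5 | 50% | 25% | 10% |
| 0.8 | 1 | 25% | 12.5% | 20% |
| 0.8 | 3 | 75% | 37.5% | 6.7% |
| 0.8 | 5 | 125% | 62.5% | 4% |

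**Step 4: what the cited 5% can and cannot supply.** The Background reports from the New Zealand service that "only 5% of patients who had been managed in the community by an ECP had an acute ED presentation within 7 days", and adds that no figure for conventional crews was provided. That is *r1* without *r0*. If *r0* were 2.5%, the excess would be 2.5 points; if 5%, zero; if higher, negative. The 5-point column treats the whole 5% as excess, which the article does not support as an estimate.

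**Step 5: a comparison channel.** The same New Zealand report gives 40% of ECP-attended patients transported to ED. Charging each of these one index ED cost would remove 0.40 / (1 − *k*) of the saving: 57% at *k* = 0.3, 80% at 0.5 and 200% at 0.8. That 40% covers all ECP-attended patients, not those who meet a protocol, so it is no estimate for Perth. It does show that returns cannot be called the main channel.

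**The case against.** The strongest reply is that the article fixes nothing. The patient-level method is offered subject to feasibility, no horizon is stated, the general cost sentence covers ED and inpatient hospital care, and the text speaks both of cost per contact and of cost per patient. A condensed article may leave horizon and sensitivity analyses to the full protocol. Most of this stands. A reader might infer that returns are deliberately excluded from both models, or that costing is confined to the index visit. The article says neither, and on the current-practice side the omission is only silence. The ECP side differs: it is defined positively as ambulance or community treatment and then equated with the model's average cost. The general sentence sets a perspective that this definition does not carry through.

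A second reply is that the study is virtual. Flagged patients still receive usual care, so the tracked returns follow usual care and would cancel if added equally to both models. This also stands. A reader might infer that costing the linked returns would reveal whether ECP care causes more of them. It would not, because no return rate after ECP care is observed. What the linked data supply is *r0* and the cost of a return, which anchor a sensitivity analysis.

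A third reply is that the magnitude has no anchor in the documents. That is correct, and the table in the working is conditional for that reason.

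**Conclusion.** The point holds in a limited form. As Phase 6 is described, the ECP-model cost cannot register a later ED visit or readmission, and neither model's listed items name these events, although the study collects them. The saving is overstated if, and only if, non-transport raises 7-day returns, with return costs taken as equal in the two models.

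The size is unknown. Under the assumed costs, a 5-point excess would take between 7% and 125% of the saving and a 2.5-point excess between 4% and 63%; with no excess the loss is nil. The upper ends need an ECP contact nearly as costly as ED care and returns costing several times an index visit.

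A reader might go further and conclude that returns are the chief threat to the saving. The documents do not show this: flagged patients who need ED care at the first attendance are also costed only at ambulance or community rates, and that channel may be larger. The change is still worth making before Phase 6 is run, because it alters what the economic comparison can conclude.

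**What to change.** In Phase 6, cost each flagged patient over a 7-day episode starting at the index attendance, matching the follow-up already planned.

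- **Current practice:** add the observed costs of linked ED re-presentations, readmissions and repeat ambulance attendances.
- **ECP model:** add the same components. Use the observed post-ED return rate as a reference scenario, noting that it leaves the saving unchanged if return costs are equal, and then a range of assumed excess rates above it.
- **Report** the excess return rate at which the saving reaches zero, so that readers can judge whether it is plausible.
- **State** that the ECP return rate is assumed because the study is virtual and cannot observe it. If the cited 5% is used, present it as a total rate to be read against the observed post-ED rate, not as an excess.

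The cost is a short text change and one more term per model. The observed terms use events already collected; only unit costs for returns and the assumed excess rates are added. The drawbacks are a little more analysis, reliance on an assumed rate, and possibly a smaller stated saving.

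### Phase 6 gives every flagged contact an ambulance or community cost only, so hospital care that flagged patients would still need is counted as an ECP saving

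*Protocol article*

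**What the plan says.** Everything at issue is in the protocol article, section Phase 6: Economic evaluation.

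- **Scope.** "Cost estimation will include costs incurred by the ambulance service, community health services and hospitals providing ED and inpatient care".
- **Current practice.** If feasible, the costing uses "patient level data relating to ED diagnosis, time in ED, hospital admission length of stay and procedures undertaken to calculate the average cost per patient". Inpatient cost is therefore part of the comparator.
- **ECP model.** "For each contact flagged as potentially being managed by an ECP", the article continues, "we will estimate the cost to provide treatment using either ambulance or community services". The rule sets no condition on what happened in the ED.
- **Average.** The next sentence reads "This will allow for an estimation of the average cost of treatment under an ECP model of care".
- **Use.** The two averages are compared to "identify any cost savings that may offset the upfront costs of providing a training programme".

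Elsewhere the article plans to record the outcomes that bear on this. Phase 1 collects ED disposition, length of stay, procedures, deaths and re-presentation up to one week. Phase 3 repeats that follow-up and adds readmission. The Statistical analysis section models admission by ECP candidate status. None of these is named as an input to the ECP-model cost.

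**The concern.** The study follows flagged patients to hospital because the flag may be wrong for some of them. Where a flagged patient was admitted and needed to be, an ECP service would have paid for its own attendance and the hospital would still have paid for the ED visit and the stay. The Phase 6 rule keeps the first cost and drops the second, while the comparator carries both.

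The error runs one way. Each flagged patient who was admitted raises the current-practice average and leaves the ECP average unchanged, so the reported saving rises with the admission share among flagged patients whether or not those admissions were avoidable. Cost-effectiveness is one of the three things the Discussion says must be established, and the saving is to be set against training costs. An inflated figure would bear directly on that decision.

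The rule also has no term for patients managed in the community who then present to an ED, although the Background cites a New Zealand report in which "only 5% of patients who had been managed in the community by an ECP had an acute ED presentation within 7 days".

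**Working it through.** The article states no cost or saving for Phase 6, so there is no figure to reproduce. The check is an accounting identity per flagged contact, followed by an illustration.

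**Inputs**
- ED visit cost = 1 (the unit).
- *R* = cost of an inpatient episode in ED-visit units. Not in the article; assumed 3, 5 and 10.
- *c* = ambulance or community cost under the ECP model. Not in the article; assumed 0.5.
- *p* = share of flagged contacts admitted. Not in the article; assumed 5%, 10% and 20%. The only admission figure given is for all Perth ED attendances (170,000/580,000 = 29.3%), which is not a rate for flagged patients.
- *v* = fraction of those admissions that ECP care would truly avert. Not in the article.

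**Formulas**
- Current practice: 1 + *pR*.
- ECP model as worded: *c*. Saving as worded: 1 + *pR* − *c*.
- ECP model with hospital cost kept for admissions not averted: *c* + *p*(1 − *v*)(1 + *R*).
- Overstatement = *p*(1 − *v*)(1 + *R*). It does not depend on *c*, and it is zero only if *p* = 0 or *v* = 1.

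**No admission averted (*v* = 0), *c* = 0.5**

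| *p* | *R* | Saving as worded | Saving with hospital cost kept | Overstatement |
|---|---|---|---|---|
| 5% | 3 | 0.65 | 0.45 | 0.20 |
| 5% | 5 | 0.75 | 0.45 | 0.30 |
| 5% | 10 | 1.00 | 0.45 | 0.55 |
| 10% | 3 | 0.80 | 0.40 | 0.40 |
| 10% | 5 | 1.00 | 0.40 | 0.60 |
| 10% | 10 | 1.50 | 0.40 | 1.10 |
| 20% | 3 | 1.10 | 0.30 | 0.80 |
| 20% | 5 | 1.50 | 0.30 | 1.20 |
| 20% | 10 | 2.50 | 0.30 | 2.20 |

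**Half of admissions averted (*v* = 0.5), *p* = 10%, *R* = 5.** Overstatement = 0.10 × 0.5 × 6 = 0.30. The saving is 1.00 as worded and 0.70 with hospital cost kept, so the overstatement halves but remains.

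**Slope.** As worded, the saving changes by *R* per unit of *p*. With hospital cost kept, it changes by *R* − (1 − *v*)(1 + *R*) = *v*(1 + *R*) − 1. The two agree only at *v* = 1. At *v* = 0 the second is −1: more admissions among flagged patients should lower the saving, yet the rule as worded raises it.

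**Re-presentation.** If each return costs one ED visit, the net term among those not admitted is (1 − *p*) × (ECP return rate − current-practice return rate). At *p* = 10% and the cited 5%, it is 0.90 × 0.05 = 0.045 if nobody returned under current practice, and zero if the rates were equal. On these assumptions it is small beside the admission term.

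**The case against.** The best defence is that the scope sentence puts hospital ED and inpatient costs into the evaluation and does not confine them to current practice. The costing is also conditional on a feasibility check, and a fuller economic plan may exist. This shows that hospital costs are meant to count somewhere. It does not rescue the rule: the stated steps give a flagged contact an ambulance or community cost and go straight to the ECP average, with no step returning hospital cost to flagged patients who were admitted. Feasibility decides whether the rule is run, not whether it is sound.

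A second objection stands in part. Some admissions may really be averted. The Background cites a South Australian report in which 60 of 1,123 ECP attendances (5.3%) were judged to have prevented an admission, and the Discussion hopes for less inpatient demand. It would therefore be wrong to treat every flagged admission as unavoidable. The 5.3% is a share of attendances, not of admissions, so it does not supply *v*; it supports varying *v*. Likewise, patients sent home from an ED also return, and the article notes that the 5% came without comparison data, so returns should not be charged to the ECP arm alone.

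A reader might infer more than the article supports:

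- **That up to 40% of flagged patients would be transported anyway.** The New Zealand 40% covers all patients attended by ECPs. The Phase 3 flag marks those meeting criteria for community management, so patients an ECP transports correspond mainly to the unflagged group.
- **That the two averages cover different patients.** The wording does not rule this out, but it states no such error.
- **That Phase 7 has the same fault.** Its section fixes no diversion rule that could be called wrong.
- **That cost would drive unsafe flagging.** Cost is not a criterion for the flag. Safety is assessed separately in Phases 3 and 4 and is named as the primary concern.

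**Conclusion.** The point holds as a biased stated rule, not as missing detail. Followed as worded, Phase 6 counts as an ECP saving the hospital care that flagged patients would still need. Per flagged contact the overstatement is the share still needing admission times the sum of ED and inpatient cost.

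The direction rests on the text alone, provided some flagged patients still need admission. The size rests on assumptions: for *R* from 3 to 10 with none averted, it is 0.20 to 0.55 ED-visit costs at a 5% share and 0.40 to 1.10 at 10%. A claim that the saving is inflated by some particular multiple is tempting from the table but is not supported. Any such multiple depends on assumed unit costs, an assumed admission share and an assumed averted fraction, none of which the article gives.

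**What to change.** Reword Phase 6 so that the same flagged patients are costed under both models.

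1. **Flagged patients who were admitted, transferred or died:** ECP-model cost = ECP attendance plus their observed ED and inpatient cost. Add a sensitivity analysis varying the fraction of admissions truly averted, from none to all; the rule as worded is then the extreme case of all.
2. **Other flagged patients:** ECP-model cost = ambulance or community cost plus the expected cost of ED re-presentation, for example starting around the cited 5% and varied.
3. **Current practice:** count the observed re-presentations of the same patients, so that returns enter both arms.
4. **Reporting:** show the admission share among flagged patients next to the saving.

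Disposition, length of stay, procedures, deaths, re-presentation and readmission are already to be collected in Phases 1 and 3, so no new data collection is needed. The cost is a few sentences, a modest amount of extra analysis and, in all likelihood, a less favourable saving.
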